### Study Assessments

Study assessments comprise three major modules (shown in Figure 2): A comprehensive baseline assessment at study intake (before the first day of EMA), an EMA module (spanning 10 days, with ten assessments per day), and an end-of-study assessment (after the last day of EMA).

**Figure 2 F2:**
[figure not shown]
Depiction of assessments within the project TempRes. The signal-contingent Ecological Momentary Assessment (EMA) module contains ten assessments per day over a course of 10 days, resulting in up to 100 single assessments per person. Displayed are the main constructs of interest in the context of the primary research question. Beyond these, the EMA module also includes assessments of mood and context variables.

Before the baseline assessment, participants generate their participant code which is used to link all modules. After the baseline assessment, they receive a short instruction concerning the app Samply Research through which the EMA module and the end-of-study assessment are controlled. After signing up and entering the participant code once, participants no longer have to open the app independently as assessments are prompted by notifications.

#### Baseline Assessment

This assessment captures socio-demographic information (such as gender, age, level of education, living situation, and employment), whether participants were recruited from the general population or in the context of their treatment at one of the two participating departments of the University Medical Center Mainz, and a concise survey of self-reported technical/digital competencies. It also includes established, psychometrically sound inventories assessing background factors as well as currently relevant stressors and domains of distress:

a. Current stressors, symptoms, and emotional states: PHQ Stress, PHQ-9, PHQ-15, GAD-7, which are all included in the Patient Health Questionnaire (48, 49), Mini Social Phobia Inventory (Mini-Spin) (50), Beck Scale for Suicide Ideation (51), Beck Hopelessness Scale BHS (52), Subjective emptiness scale (SES) (53), Short Defeat and Entrapment Scale (54, 55), Brief Reasons for Living Inventory (BRFL) (56)b. Social factors: Brief Social Support Scale BS-6 (57), UCLA 3-Item Loneliness Scale (58, 59), Experiences in Close Relationships (ECR-RD-8) (60), Interpersonal Needs Questionnaire (INQ) (61)c. Individual differences and personality characteristics: Scale Optimism-Pessimism-2 (SOP2) (62), Emotional Regulation Questionnaire (ERQ) (63), Theoretical Depressive Experiences Questionnaire-12 (TDEQ-12) (64), Big Five Inventory (BFI-10) (65), OPD-Structure Questionnaire (OPD-SQS) (36), Theoretical Depressive Experiences Questionnaire TDEQ-12 (64)d. Experiences while growing up: Recalled parental rearing behavior (66), Childhood Trauma Questionnaire CTQ (67)

In addition to these inventories, the assessment includes questions about pandemic-related stressors (e.g., current quarantine). Although the study does not aim to examine mental health in relation to the COVID-19-pandemic, this context cannot be ignored at the present time.

#### EMA Module

In Sample Research, notifications are planned for all 100 scheduled assessment of the EMA module and for the end assessment. The former are sent via push messages at preset times (pseudo-randomized intervals between 8 a.m. and 10 p.m., with a minimum interval of 45 min) to each participant. Each push message contains the same link to the EMA survey on SoSci Survey. Respondents need only click on the link and answer the questionnaire in their browser.

Each assessment includes fewer than 25 items in total. All items except the context variables will use the same response format (1 = “not at all” to 7 = “very”). Context items will assess where participants are currently (e.g., at home, at work) and whether they are alone or have company. Suicidal ideation will be measured using three items adapted from the Beck Scale for Suicide Ideation (51) (“I have a wish to die,” “I have a wish to live,” “I have a wish to kill myself”). As suicidal ideation is not a uniform construct (see Introduction), this kind of assessment allows for the differentiation of a wish to die (i.e., passive death wishes), wish to live, and wish to end one's life (i.e., active suicidal ideation). It will be placed in the middle of the administered items to reduce participants' reactivity to it. The same applies to defeat, entrapment [assessed with two items each, drawn from the German Defeat Scale (DS-d) (68) and the German Entrapment Scale (ES) (69)] and loneliness [assessed with two items, adapted from Kleiman, Turner (19)]. Additional items include positive and negative affect, which will be measured using items drawn from the German PANAS-X (70, 71). Lastly, two items drawn from the Beck Hopelessness Scale (52) will assess hope/hopelessness.

Items were chosen based on their psychometric properties (e.g., those with the highest factor loadings of their respective scales in the questionnaire long form). In cases where items were drawn from longer scales, we checked whether their wording needed to be adapted to the “here and now.” However, this was not necessary as the original questionnaires communicated the time period of interest as part of the instruction rather than as part of the items themselves. The sequencing of items does not change throughout the study.

#### End Assessment

The end assessment repeats the most important symptom measures from the start assessment. It includes questions about special events in the last days that the researchers should be aware of when interpreting the data (answered via free text). It also assesses the acceptance of the EMA module (regarding both the contents and the method) and the perceived intrusiveness of the EMA protocol.

### Data Structure and Analyses

Analyses will be conducted using R (72) and mainly using the packages esmpack (73), lme4 (74), and lmerTest (75).

The special survey methodology implicates a longitudinal and nested data structure in which the measurement points (Level 1) are nested within days (Level 2) which are in turn nested in participants (Level 3). This is why the main analyses will build on linear mixed models, a technique in which separate regression functions are estimated for each cluster. Such models expand the standard regression model by random effects that allow for the investigation of person-level differences in model coefficients [see e.g., (76, 77)]. Models will include random intercepts and random slopes (i.e., the deviations of participants' values from the respective group mean) and account for autocorrelation. Moderation effects will be probed by creating the product of the mean-centered variables of interest (entrapment and loneliness). In the case of statistically significant interaction effects, the steepness of the regression line on different values of the moderator (i.e., entrapment) will be visualized (e.g., for the sample mean and the sample mean +/– one standard deviation).

The primary outcome is suicidal ideation. Its operationalization via three items allows for tests of construct validity and reliability [e.g., as nested α (78)]. Secondary outcomes are entrapment and loneliness.

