Hypothesis 1: According to premise 6 of the IMV model (detailed in 13), individuals who have intentionally self-harmed in the past report higher levels of the motivational phase variables (entrapment, loneliness, and suicidal ideation) than those who have not done so.Hypothesis 2: Motivational phase variables (entrapment, loneliness, and suicidal ideation) vary over time.Hypothesis 3: Entrapment is positively associated with suicidal ideation:Hypothesis 3.1 Feelings of entrapment are positively associated with suicidal ideation.Hypothesis 3.2 The relationship between entrapment and suicidal ideation is moderated by loneliness, i.e., it is particularly strong if people also feel lonely.

The secondary research goal concerns the exploration of the role of personality functioning. Since this part of the project cannot directly relate to previous studies with similar methodology, the hypotheses are less concrete: First, we will explore associations of personality functioning with established risk and protective factors from the pre-motivational phase (e.g., we expect impaired personality functioning to be associated with childhood abuse and neglect and with previous self-harm). Second, the level of personality functioning will be tested as a background factor, in the sense that greater impairments are assumed to be associated with higher levels of the motivational phase variables. However, it could also play a role as a moderator within the motivational phase: motivational moderators are defined as “factors that, when present and protective, allow the trapped individual to see alternatives, a more positive future and less pain” (12). Respective constructs included implicit and explicit attitudes as well as negative self-appraisals, both of which conceptually overlap with measures of personality functioning such as the OPD-Structure Questionnaire (OPD-SQS) (36). In addition, studies have suggested an intermediate role of personality functioning, for instance, it linked childhood abuse and neglect with mental distress later in life in a cross-sectional population study (37) and with inhibition difficulties in an experimental go/no-go task (38) in patients with depressive and personality disorders and healthy control participants.

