#### Power and Sample Size Considerations

Considerations of power and sample size in intensive longitudinal studies must include both within- and between-person sources of variation. These sources of variation are influenced differently by the number of measurement points and the number of participants included in the study, complicating calculations (76). This might be one of the reasons why reports of intensive longitudinal studies seldom include power calculations or sample size justifications (82). We conducted general power and sample size calculations for a longitudinal study design (83) targeting outcome variation within participants, in which

$$\begin{array}{l} Power=\frac{n\;x\;m}{1+\left(m-1\right)\;x\;ICC} \end{array}$$

with n indicating number of participants and m indicating measurement points per participant. The intraclass correlation (ICC) states how much variance of a variable is due to temporally stable factors, i.e., between-person variability as opposed to within-person variability (76). This formula can be transformed the following way:

$$\begin{array}{l} n=\frac{Power\;x\;\left(1+m-1\right)\;x\;ICC}{m}\; \end{array}$$

In previous studies, the ICC of the motivational phase variables of interest ranged between 0.54 [for entrapment (24)] and 0.67 [for suicidal ideation (19)], so we chose the upper bound for our calculation. With a desired power level of 80%, 60 expected assessments per person (see above), and an ICC of 0.67, we would need 54 participants overall.

However, given the fact that the estimated compliance rate is not guaranteed and we aim to test several hypotheses, e.g., regarding group differences concerning pre-motivational phase variables, we plan to recruit more participants than the calculated minimum sample size. Therefore, we plan to assess about 50 patients and 100 participants from the general population (as recruitment of the latter is less costly in terms of research staff's time). Empirical investigations of the single hypotheses, including cross-level interactions, will include more specific, simulation-based power analyses making use of resources such as the recently developed app PowerAnalysisIL (84).

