However, there are several limitations. As mentioned, low proportions of individuals reporting suicidal ideation, especially in non-clinical populations, present a challenge to empirical research on associated risk and protective factors. The present study tries to address it by combining different samples. However, if responses on the respective items yield a highly skewed distribution, it might be necessary to adapt the analysis strategy (either by calculating logistic mixed-effects models or by summarizing instances of any level of suicidal ideation). Further, anonymity in responses and the absence of incentives/guaranteed reimbursement might hamper compliance and implicate comparatively low participation rates. As the EMA module only assesses suicidal ideation, the study cannot give insight into time-varying risk and protective factors underlying suicidal behavior. The exclusion of acutely suicidal individuals (which we deemed necessary for safety reasons) represents a further limitation as it means that the resulting findings might not apply to those individuals with the highest risk. In future research with the appropriate resources, they should be included, and their responses should be closely monitored (41). Indications of acute risk should also receive some sort of reaction. However, as it is unclear whether pop-up notifications are read and perceived as helpful in case of acute risk (47), ideally, trained staff should be available to reach out to participants, e.g., by phone.

Lastly, it will not be feasible to recruit a representative sample of the population or of the patients treated at the participating departments. There might be specific self-selection effects (including motivational aspects and expectations of the study) which we can neither assess nor statistically control for. However, we intend to compare study participants' characteristics (e.g., gender distribution, age, level of education, symptom burden) with both routine data collected on all consecutive patients treated at the clinics during the trial period and representative survey data of the general population.

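### The stated test of Hypothesis 3.2 has no curvature term: if entrapment and loneliness correlate, part of any convex entrapment effect would appear as moderation by loneliness

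*Protocol article*

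**What the plan says.** Hypothesis 3.2 in the Introduction reads: "The relationship between entrapment and suicidal ideation is moderated by loneliness, i.e., it is particularly strong if people also feel lonely". The Abstract presents this interaction as the test of a core assumption of the IMV model.

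The section Data Structure and Analyses sets the model class ("Models will include random intercepts and random slopes", with allowance for autocorrelation) and the test: "Moderation effects will be probed by creating the product of the mean-centered variables of interest (entrapment and loneliness". It does not say whether centring is at the sample mean or the person mean. A decision step follows. "In the case of statistically significant interaction effects", simple slopes are plotted at the sample mean and one standard deviation either side. That sentence calls entrapment the moderator ("the steepness of the regression line on different values of the moderator (i.e., entrapment) will be visualized"), whereas Hypothesis 3.2 gives that role to loneliness. The product term is the same either way, so the test is unaffected, but the two places should be reconciled.

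No squared term, smooth term or check of functional form is mentioned anywhere. The only analytic fallback is in Discussion of Strengths and Limitations: "if responses on the respective items yield a highly skewed distribution, it might be necessary to adapt the analysis strategy". It moves to a logistic mixed model or an any-ideation outcome. It changes the outcome and leaves the predictor side as it was.

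**The concern.** A product of two correlated variables is itself correlated with the square of each. If the effect of entrapment steepens at high levels and the model has no term for that, the product takes up part of the steepening even when loneliness moderates nothing. With a positive correlation and a convex effect, the artefact has the sign that Hypothesis 3.2 predicts.

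A significant product would then be plotted and read as support for a motivational moderator, although it might show only that high entrapment has a steeper effect. This is the study's main theoretical test, and nothing in the article would let a reader tell the two explanations apart.

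**Working it through.** **Inputs from the article.** Planned sample: 150 (50 patients, 100 general population). Expected assessments per person: 60. ICC: 0.54 for entrapment, 0.67 for ideation. All are in Power and Sample Size Considerations.

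**Assumed, because the article does not give them.** The entrapment–loneliness correlation r (main range 0.3 to 0.5), the entrapment-squared coefficient c in SD units, and a two-sided 5% level.

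**The plan's own figure.** The stated minimum of 54 participants reproduces: 80 × (1 + 59 × 0.67)/60 = 54.04, with power entered as 80. It does not address the interaction, so there is no stated figure to check for this point.

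**Step 1, share of curvature taken up by the product.** Let E (entrapment) and L (loneliness) be centred, standardised and bivariate normal. Let the true model contain E, L and cE², with no interaction. The odd moments vanish, so E and L are uncorrelated with E² and EL. Leaving out E² then gives the product a coefficient of c × cov(E², EL)/var(EL).

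- cov(E², EL) = 3r − r = 2r
- var(EL) = (1 + 2r²) − r² = 1 + r²
- share = 2r/(1 + r²)

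| r | 0 | 0.1 | 0.3 | 0.5 | 0.7 |
|---|---|---|---|---|---|
| share | 0 | 0.20 | 0.55 | 0.80 | 0.94 |

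The variables are already centred in this derivation, so mean-centring does not remove the effect.

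**Step 2, false-positive rate at the planned size.** Simulation of 150 people × 60 prompts with no true interaction, 400 runs per cell, predictor ICC 0.54 and outcome ICC about 0.67. Data had random intercepts and slopes; the analysis used person-level intercepts and person-clustered standard errors.

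| Model and centring | c | r = 0 | r = 0.3 | r = 0.5 | r = 0.7 |
|---|---|---|---|---|---|
| Product only, grand mean | 0.02 | 4% | 23% | 44% | 59% |
| Product only, grand mean | 0.05 | 4% | 80% | 98% | 100% |
| Product only, person mean | 0.05 | 5% | 52% | 89% | 98% |
| With E² and L², grand mean | 0.05 | – | 6% | 5% | 6% |

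At c = 0.05 with grand-mean centring, the mean product estimates were 0.027, 0.039 and 0.047 at r = 0.3, 0.5 and 0.7. The closed form gives 0.05 × 0.55 = 0.0275, 0.05 × 0.80 = 0.040 and 0.05 × 0.94 = 0.047. With c = 0 the rejection rate was about 5–8% at every r, so correlation alone does no harm.

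A second, person-centred simulation set curvature at 0.4% of within-person outcome variance. It gave 69% (r = 0.3) and 98% (r = 0.5), falling to 4–7% with squared terms. With only 30 informative people the rates were 23% and 38%, against 5–7%.

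**Step 3, price of the squared terms.** Regressing EL on E² and L² gives R² = 4r²/(1 + r²)². The standard error of the product therefore rises by (1 + r²)/(1 − r²): 1.09/0.91 = 1.20 at r = 0.3 and 1.25/0.75 = 1.67 at r = 0.5.

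**Step 4, limit of the squared terms.** Ideation is scored from 1 to 7 (EMA Module: "All items except the context variables will use the same response format"), and low rates are expected in the community. A further scenario had linear latent effects, no latent interaction and a floor on the outcome (assumed at +0.5 on the latent scale). At r = 0.5 the linear model rejected in 100% of runs without squared terms and still in 73% with them. Across the grand-mean settings tried, the figures were 85–100% and 46–88%.

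In a small ordinal-model check (60 runs, about 80% of outcomes at the floor, c = 0.1), curvature gave 25–50% false products without squared terms and 3–10% with them. Sixty runs are too few to establish error control, but the direction agrees.

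**The case against.** The strongest reply is that this is an ordinary moderation test described in a condensed article. Functional-form checks usually sit in an analysis plan, which is not shown here, and the article does not exclude squared terms. Both premises are assumed: no entrapment–loneliness correlation is reported and no curved effect is asserted. The same remark could be made about many product-term tests.

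Most of this stands. A reader might infer that any curved entrapment effect would be read as moderation, or that the planned test is invalid. The article supports neither. The share is zero at r = 0 and below one for every r below one, and a concave effect would bias against Hypothesis 3.2. Without curvature the test keeps roughly its nominal level. The simulated rates follow from the chosen c, r and centring and do not predict what this study will find.

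What does not stand is that nothing has been fixed. The article settles the product, the significance trigger and the plot, and its one fallback alters only the outcome. A positive r is also plausible from the design. Hypothesis 1 expects both variables to be higher in people with past self-harm, and patients are pooled with the general population to create variation. If patients were 1 to 1.5 within-group SD higher on both (an assumption), the 1:2 mix alone would give r = (2/9)d²/(1 + (2/9)d²), about 0.18 to 0.33, with no correlation inside either group.

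The objection that squared terms could reassure falsely under a floor is also right, and it shapes the fix.

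**Conclusion.** The point holds as an unguarded risk to how a significant product would be interpreted, not as a demonstrated error. If r lies between 0.3 and 0.5, then 55% to 80% of a convex entrapment-squared coefficient would appear as a positive product. At the planned size, the simulated false-positive rate over that range of r ran from about 23% to 98%.

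These figures rest on assumed r and curvature, approximately normal predictors, a two-sided 5% level, and clustered standard errors in place of the planned mixed model. The closed form is exact under its assumptions; the rates are illustrative. This is a cheap improvement that protects the main conclusion. It is not a reason to replace the test.

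**What to change.** Keep the product model as the main test of Hypothesis 3.2, and add to Data Structure and Analyses:

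- A pre-specified robustness fit of the same model with entrapment squared and loneliness squared added, using the same centring as the main test (and stating which centring that is).
- The same fit in the outcome model that the Discussion already foresees for skewed ideation, because squared terms in the linear model do not remove a product created by the floor.
- A reading rule. If the product estimate shrinks materially towards zero in these fits, report that moderation by loneliness cannot be separated from a curved entrapment effect. State in advance how much shrinkage counts as material. Loss of significance alone should not be read as refutation, and a product that persists only in the linear model should not be read as confirmation.

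The cost is a few extra fits on data already being collected and a short addition to the text. The statistical price is a standard error for the product about 1.20 (r = 0.3) to 1.67 (r = 0.5) times larger, which is why these fits should be robustness checks and not the main test.

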#### Expectations Regarding Compliance

Review articles of previous EMA studies found compliance rates of 79% across samples (79) and 77% in studies focusing on self-harm and suicide (26). However, as suicidal ideation, the main construct of interest, has been shown to fluctuate substantially (19, 80), we chose a sampling design with more assessments per day and a longer assessment period than most of the summarized research (e.g., respective mean values were six assessments per day over the course of 1 week (79). Therefore, we expect compliance rates in the present study to be lower, i.e., around 60 of 100 assessments. Studies achieved higher compliance rates when using incentives (79). In this study, we do not communicate a certain target compliance rate to participants (e.g., the completion of >50% of assessments) as we do not want to motivate them to answer prompts without regard to the questions/answering truthfully. However, they are informed that all participants who stay with the study for 10 days are—at the very end—given the opportunity to enter a raffle (of 15€-shopping vouchers for a supermarket). After data collection is completed, individual participants' data might be excluded from the analyses if the free text answer in the end assessment contains information about events that complicate the interpretability of their responses in a substantial way (e.g., technical dysfunction of their mobile phone). Such cases will be made transparent in the study reports. It is also common practice to include only individuals with a certain percentage of completed assessments in the analyses. However, all thresholds (e.g., 15%) applied in this context are somewhat arbitrary. Therefore, we will follow recommendations to only use them in combination with sensitivity analyses using the whole sample, in order to check whether the resulting findings are robust (81). Predictors of signal compliance will also be investigated (e.g., age, gender, symptom burden, and technical/digital competencies).

